## Discussion

The present study is designed to evaluate the effects of 18 sessions of LLLT over cognition, in patients with chronic moderate and severe TBI. Our primary hypothesis is that the sessions of active LLLT will improve attention (at least 1 SD) measured by Stroop test compared to the placebo group (sham LLLT). Our secondary hypothesis is that the active group will improve in all domains assessed by the neuropsychological battery, including cognition and mood, compared to placebo group.

LLLT can modulate many biological effects penetrating the scalp into the brain [25], playing a role improving the outcome of the patients in two different ways, depending on the stage of the trauma. In the acute phase after TBI, the initial neuronal injury occurs instantly and oftentimes causes irreversible damage to the central nervous system, due to impairment of neuronal cell functions, including mitochondria, and glia cells [18, 58]. The disruption of neuronal circuitry causes loss of connectivity between different areas of the brain and can negatively impact neural regeneration, leading to dysfunctional interactions. In the secondary stage after the trauma, other changes may occur, including release of neurotransmitters, decreased glucose utilization, lactic acid accumulation, reduced activity of ATP-reliant ion pumps, increased release of glutamate, Ca2 + −induced depolarization, and excitotoxicity [21, 58].

Previous studies showed improvement on cognition including attentional process and episodic memory after repetitive sessions of LLLT in patients with TBI [17, 37]. It seems that the LLLT decreases the inflammatory response, helping the neuroprotection after TBI. This process leads to increases on the ATP, cellular energy, and blood flow, decreasing the metabolic process. In summary, the LLLT seems to increase the intercellular synapses, acting as a possible treatment after acute and chronic TBI [37, 59–61].

Other studies reported the effects of the LLLT in another sample. Lampl et al. [34] used the LLLT in patients with ischemic stroke and showed that infrared wavelength therapy was safe and effective in the experimental group compared to the control groups when treatment was started 24 h after the onset of stroke. Another study with psychiatric patients showed that seven (out of ten) patients with severe cases of depression and anxiety presented symptom remission after two weeks elapsed with four LLLT applications in the prefrontal region, which did not occur with the control group [62]. Likewise, LLLT has been demonstrated as a safe and effective technique in significantly improving the memory, attention, and mood performance of healthy people [63]. Overall, we expect that our trial can complement previous findings, as an effective low-cost therapy to improve cognitive sequel in patients with chronic TBI.

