### Objective

The aim of this study is to evaluate inhibitory attentional control after 18 sessions of active LLLT and compare with the placebo group (sham LLLT). Our exploratory analysis will evaluate verbal and visuospatial episodic memory, executive functions (working memory, verbal and visuospatial fluency, attentional processes), and anxiety and depressive symptoms.

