### Sample size

Based on the previous pilot study [37] that analyzed the cognitive function of patients with TBI after repetitive sessions of RED/Near-infrared LED treatment. Considering the improvement on Stroop test of 1 standard deviation (SD) related to the baseline, the level of significance of 0.05 and the power of 80%, 16 patients per group was estimated. Considering the rate of 15% of drop-outs, we added two participants per group, ending with a total sample of 36.

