### Randomization

All eligible recruited patients will be randomly divided into two groups with a 1:1 ratio and blocks of four and six performed by the co-investigator through the randomization list (randomization.com). The randomization list will be kept in safe storage with the co-investigator responsible for the stimulation sessions. She will provide the allocation concealment assignment for the patients. No information about the assigned group will be given for the patient or to the research assessor.

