### Statistical analysis

Intention-to-treat and per-protocol analyses will be performed for the primary and secondary outcomes. Missing data will be analyzed with regression imputation, considering the confounders (months of the trauma, years of age, schooling years, and depressive symptoms). Patients that did not receive 60% of the total stimulation will be considered non-adherent and analyzed as per-protocol.

Means and standard deviation will be used to represent data with normal distribution and medians and quartiles to describe non-normally distributed data. Two-way ANOVA (2 groups × 3 times) with repeated measures (for parametric variables) or the Kruskal–Wallis test (for non-parametric variables) will be used for the analysis of the TLT effects obtained in the three timelines: baseline, one week, and three weeks after the intervention. The Bonferroni correction for multiple comparisons will be employed as a post-hoc test. The effect size will be calculated based on the difference between means of the pre-intervention and post-intervention evaluations and will be expressed with respective 95% confidence intervals. Parametric Student’s t-test or a Mann–Whitney *U* test for non-parametric data will be employed to assess between-group (active and sham helmet) differences in age, height, weight, and body mass index (BMI), time of TBI injury, level of education, and Glasgow Coma Scale at admission on the emergency room. For all effects, a *p* value < 0.05 will be considered indicative of statistical significance. The data will be organized and tabulated using the Statistical Package for the Social Sciences (SPSSv.19.0).

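### The secondary scores are called exploratory, yet they carry a hypothesis against sham and a p < 0.05 significance rule with no error control across outcomes

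*Protocol article*

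**What the plan says.** The protocol article gives the same set of outcomes three different roles.

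- **Objective** (and Abstract): exploratory. "Our exploratory analysis will evaluate verbal and visuospatial episodic memory", followed by executive functions and anxiety and depressive symptoms.
- **Secondary outcomes**: the same domains are listed as secondary outcomes, with no order and no key secondary outcome.
- **Discussion**: a directional hypothesis in comparison with placebo. "Our secondary hypothesis is that the active group will improve in all domains assessed by the neuropsychological battery".

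The Statistical analysis section plans intention-to-treat and per-protocol analyses for both primary and secondary outcomes. Each outcome is analysed by a 2 × 3 repeated-measures ANOVA or a non-parametric alternative. The section closes with "For all effects, a *p* value < 0.05 will be considered indicative of statistical significance". Bonferroni is named once, as a post-hoc test, directly after the ANOVA sentence.

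The Sample size section rests on the Stroop test alone: "Considering the improvement on Stroop test of 1 standard deviation (SD) related to the baseline".

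**The concern.** Testing exploratory scores without adjustment is acceptable as long as they are reported as exploratory. Here the rule that decides what counts as significant is not limited to the primary outcome, and a hypothesis of benefit is attached to the remaining outcomes. Read in its place, the Bonferroni sentence covers pairwise comparisons within one outcome's ANOVA and leaves the number of outcomes uncontrolled.

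The hypothesis covers every domain, but no rule says what result would confirm it. Nothing in the article says whether all domains must succeed, or how a result in only one of them is to be described. A chance result on one memory or mood score could then be declared significant under the stated rule and placed beside the stated hypothesis. In a trial of 36 patients sized only for the Stroop test, readers could not tell such a result from a real effect.

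**Working it through.** **1. The plan's own figure.** The article states no familywise error rate and no number of secondary tests, so there is no such figure to reproduce. The one relevant figure is the sample size: "the level of significance of 0.05 and the power of 80%, 16 patients per group was estimated". With a difference of 1 SD, two-sided 0.05 and 80% power, the normal approximation gives n = 2 × (1.960 + 0.842)² / 1² = 15.7, so 16 per group. This agrees, and it confirms that the design was sized on one test of one outcome.

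**2. Number of secondary tests (m).** This has to be counted.

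- From Secondary outcomes, by domain: verbal memory, visuospatial memory, working memory, verbal fluency, visuospatial fluency, attention, anxiety, depression. m = 8.
- From Neuropsychological assessment, one score per instrument other than Stroop: BDI-II, BAI, TMT, COWAT, Five-point, SDMT, RAVLT, number-letter sequence, Digit Span, ROCF. m = 10.
- From the same section, by score: BDI-II 1, BAI 1, TMT 2, COWAT 2, Five-point 2, SDMT 1, RAVLT 4, number-letter sequence 1, Digit Span 2, ROCF 3. The sum is 19. This is my count; RAVLT list B would make it 20.

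**3. Assumptions.** There is no true effect on any score. Each score has one between-arm test, two-sided at 0.05 (sidedness is not stated). A false benefit for active treatment then has probability 0.025 per score. The correlation ρ between scores is not given, so a common value is assumed and varied.

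**4. Formulas.**

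- Independent, either direction: 1 − 0.95^m. For m = 8, 10 and 19: 0.337, 0.401 and 0.623.
- Independent, favouring active: 1 − 0.975^m. For m = 8, 10 and 19: 0.183, 0.224 and 0.382.
- Common correlation ρ: write each test statistic as √ρ·U + √(1−ρ)·E, with U shared and E separate standard normal variables. The chance is one minus the average over U of q(U)^m, where q(U) is the conditional probability that one statistic does not cross ±1.96 (or +1.96 for benefit only).

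**5. Results.**

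| Tests | Measure | ρ = 0 | ρ = 0.3 | ρ = 0.5 | ρ = 0.7 |
|---|---|---|---|---|---|
| 8 | any p < 0.05 | 34% | 30% | 25% | 19% |
| 8 | false benefit | 18% | 15% | 13% | 10% |
| 10 | any p < 0.05 | 40% | 35% | 29% | 21% |
| 10 | false benefit | 22% | 18% | 14% | 11% |
| 19 | any p < 0.05 | 62% | 53% | 41% | 28% |
| 19 | false benefit | 38% | 27% | 20% | 14% |

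As a check, the planned 2 × 3 repeated-measures ANOVA was simulated for 19 scores, with 18 patients per arm and an assumed within-patient correlation of 0.6. The group-by-time test alone gave at least one p < 0.05 in 62% of trials at ρ = 0 and 41% at ρ = 0.5, in line with the table.

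**The case against.** The strongest defence is that the article names one primary outcome, sizes the trial on it, and twice calls the rest exploratory. Unadjusted testing below a single primary outcome is common practice, and an article may leave a multiplicity scheme to a fuller document. The hypothesis stands in the Discussion and may express only an expectation. Much of this is sound: the lack of an adjustment scheme would not by itself be a fault. What it does not answer is the sentence that is present, which declares significance for all effects and so overrides the exploratory label.

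Read literally, the hypothesis requires every domain to improve. Such a joint rule would need no adjustment, and the at-least-one error rate would not be its error rate. That is correct, but the article states no joint rule and tests each effect singly.

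Four stronger readings are tempting, and the article does not support them.

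- A reader might infer that a false positive is likely. A chance above 50% needs about 19 scores with weak or no correlation. The article gives neither the count nor the correlation.
- A reader might take the 62% as the chance of a spurious benefit. It counts both directions; under the same assumptions, the figure favouring active is 38%.
- A reader might count all three ANOVA effects. The time effect, pooled over arms, does not compare treatments. Counting a group or a group-by-time effect would raise the simulated figures for 19 scores to 86% (ρ = 0) and 65% (ρ = 0.5), but an omnibus F-test shows no direction, and the article does not say that either effect would be claimed as efficacy.
- A reader might conclude that a single significant score will be presented as efficacy. The article does not say so; its rules only leave this open.

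**Conclusion.** The point holds as an inconsistency in stated rules. Outcomes labelled exploratory are given a hypothesis against sham and a significance threshold, with no error control across them.

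For at least one p < 0.05 in either direction, the size is about 34% (8 tests) to 62% (19 tests) if independent, and 25% to 41% at correlation 0.5. For at least one false benefit it is about 18% to 38%, and 13% to 20% at correlation 0.5. At that correlation, the false-benefit figures are five to eight times the 2.5% that applies to one such test. They rest on my counts of the tests, two-sided testing, one between-arm test per score, and assumed correlations. Testing a second analysis set can only raise the chance of at least one false positive.

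The primary Stroop analysis is untouched, so this concerns how secondary results may be claimed and does not undermine the trial's main test.

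**What to change.** - **Statistical analysis:** restrict the p < 0.05 significance claim to the primary between-arm Stroop contrast. Report every other score as a between-arm difference with a 95% confidence interval, labelled exploratory and without a claim of significance. The section already plans 95% intervals, but for effect sizes based on pre-to-post differences, so the between-arm contrast must be named.
- **Secondary outcomes and Discussion:** reword both to match the Objective, so that the other domains are described as exploratory and no longer as a hypothesis to be confirmed.

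This takes a few sentences, with no new data and no change in sample size. No adjustment across scores is needed once no significance is claimed for them. The cost is that an isolated secondary p value can no longer be presented as a finding. Trial status describes inclusion as ongoing, so at the time of the article the change could still precede the final analysis.

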## Trial status

The randomization of patients was started on January 2015. The inclusion of participants is ongoing, with 12 patients completing the assessment, four patients in the second assessment and two patients in the first assessment. We expect to conclude the study by 5 October 2018.

## Abbreviations

AP-1: Activator protein 1
ATP: Adenosine triphosphate
BAI: Beck Anxiety Inventory
BDI-II: Beck Depression Inventory II
BMI: Body mass index
CCO: Cytochrome c oxidase
CONEP: National Commission for Research Ethics
CONSORT: Consolidated Standards of Reporting Trials
COWAT: Controlled Oral Word Association Test
CREB: cAMP Response Element-Binding Protein
CT: Computed tomography
DNA: Deoxyribonucleic acid
DS: Digit span
DSST: Digit Symbol Substitution Test
GCS: Glasgow Coma Scale
HIF-1: Hypoxia inducible factor
LED: Light emitting diode
LLLT: Low-level laser therapy
MRI: Magnetic resonance imaging
NF-j B: Nuclear factor Kappa B
NIBS: Non-invasive brain stimulation
NO: Nitric oxide
RAVLT: Rey Auditory Verbal Learning Test
RCT: Randomized controlled trial
Ref-1: Redox factor-1
RNA: Ribonucleic acid
ROCF: Rey-Osterrieth Complex Figure Test
ROS: Reactive oxygen species
SDMT: Symbol Digit Modalities Test
SPIRIT: Standard Protocol Items: Recommendations for Interventional Trials
TBI: Traumatic brain injury
TMT A and B: Test Trail Making form A and B
WAIS III: Wechsler Adult Intelligence Scale III
